#### Main RCT summary

All adult patients presenting at the trial centres with an acute fracture of the distal tibia are potentially eligible to take part in the trial. The broad eligibility criteria will ensure that the results of the study can readily be generalised to the wider patient population. A computer-generated randomisation sequence, stratified by centre and age, will be produced and administered independently by a secure web-based service. Randomisation will be on a 1:1 basis to either intramedullary nailing or ‘locking’ plate fixation. Both of these operations are widely used within the NHS and all of the surgeons in the chosen centres will be familiar with both techniques.

Baseline demographic data, radiographs and pre-injury functional data using the DRI and the OMAS Questionnaire will be collected. The patients will also be asked to fill out the EuroQol EQ-5D health-related quality-of-life questionnaire twice at baseline; once to indicate their typical preinjury health status and a second time to indicate their current ‘postinjury’ status.

A research associate will perform a clinical assessment and record any early complications at 6 weeks, and a radiograph will be taken. A further clinical assessment and radiograph will also be taken at 12 months postoperatively to detect late complications. Functional outcome, health-related quality of life and resource-use questionnaires will be collected at 3 months, 6 months and 12 months postoperatively.

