## Outcome measures

The primary outcome measure for this study is the *DRI*.^16^ The DRI score is a validated questionnaire that is self-reported (filled out by the patient). It consists of 12 items specifically related to function of the lower limb. This data will be collected at baseline, 3, 6 and 12 months postoperatively (table 1). The DRI has been proven to be a robust and practical clinical and research instrument, with good responsiveness and acceptability for assessment of disability caused by impairment in the lower limb.

**Table 1 BMJOPEN2015009162TB1:** Follow-up measures

Time point data collection	
Baseline	DRI, OMAS, EQ-5D *preinjury*, *EQ-5D current* and radiographs
6 weeks	Complication records, radiographs and operative record
3 months	DRI, OMAS, EQ-5D, record of complications/rehabilitation or other interventions and resource-use questionnaire
6 months	DRI, OMAS, EQ-5D, record of complications/rehabilitation or other interventions and resource-use questionnaire
12 months	DRI, OMAS, EQ-5D, radiographs, record of complications/rehabilitation or other interventions and resource-use questionnaire

DRI, Disability Rating Index; OMAS, Olerud and Molander Ankle Score.

The secondary outcome measures in this trial:

*OMAS* is a self-administered patient questionnaire. It is a good outcome tool for assessing symptoms after an ankle fracture. The score is based on nine different items: pain, stiffness, swelling, stair climbing, running, jumping, squatting, supports and work/activities of daily living.^19^ The scoring system correlates well with parameters considered to summarise the results after this type of injury and is therefore recommended for use in scientific investigations.

*EQ-5D* is a validated, generic health-related quality-of-life measure consisting of five dimensions, each with a 3-level answer possibility. Each combination of answers can be converted into a health utility score.^20^ It has good test–retest reliability, is simple for patients to use and gives a single preference-based index value for health status that can be used for broader cost-effectiveness comparative purposes.

*Complications*: All complications will be recorded, including mal-union, delayed/non-union, infection, wound complications, vascular and neurological injury, and venous thromboembolism. A record will also be kept of any other surgery required in relation to the index fracture, including removal of any metalwork.

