## Sample size

The minimum clinically important difference (MCID) is eight points on the primary outcome (DRI) measurement scale. The DRI is a 12-question, patient reported, functional outcome measure (physical exercise or sports, running, heavy physical work, heavy lifting, carrying a bag, leaning over a wash-stand, making a bed, moderate physical work, walks, mounting stairs, sitting still more than briefly and dressing or undressing) converted to a 100-point scale where ‘0’ represents normal function and ‘100’ represents complete disability. At an individual patient level, a difference of eight points represents the ability to climb stairs or run, with ‘some difficulty’ versus with ‘great difficulty’. At a population level, eight points represents the difference between a ‘healthy patient’ and a ‘patient with a minor disability’. Eight points also corresponds approximately to the clinically worthwhile benefit identified in other studies and the difference between treatment group means in our pilot study.

The SD of the DRI in our pilot study was approximately 20 points; the sample size has also been estimated for a larger and smaller SD to obtain an indication of the sensitivity to changes in this parameter. Assuming the distribution of DRI in the study populations to be approximately normal, which is consistent with assumptions made for other reported trials using DRI as the primary outcome measure, table 2 shows the total trial sample size with two-sided significance set at 5% for various scenarios of power and sample SD.

**Table 2 BMJOPEN2015009162TB2:** Sample size at variable power and SD

	Power	
SD	80%	90%
15	112	150
20	198	**264**
25	308	412

Bold typeface indicates the actual sample size chosen for this trial.

The bold figure of 264 patients represents the most likely scenario, based on our current knowledge, for 90% power to detect the selected MCID. Allowing a margin of 20% loss during follow-up, this gives a figure of *320 patients in total*. Therefore, 160 patients randomised to each group will provide 90% power to detect a difference of eight points in DRI at 6 months with 90% power at the 5% level.

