As discussed earlier, the stratified randomisation procedure will ensure a balance in recruiting centres between test treatments and as we anticipate that any individual surgeon will operate on no more than 2–3 patients enrolled in the trial, we do not expect surgeon-specific effects to be important in this study. However, in addition to the unadjusted analysis (t tests), we will also undertake regression analyses to adjust for any imbalance between test treatment groups in patient age or gender. The fixed effects analysis (linear regression model) will also be generalised by adding a random effect for recruiting centre to allow for possible heterogeneity in patient outcomes due more generally to the recruiting centre. DRI data will be assumed to be normally distributed during modelling, but subsidiary analyses may also be undertaken after appropriate variance-stabilising transformation. The primary focus will be the comparison of the two treatment groups of patients, and this will be reflected in the analysis, which will be reported together with appropriate diagnostic plots that check the underlying model assumptions. Treatment effects will be presented, with appropriate 95% CIs, for both the unadjusted and adjusted analyses.

Temporal patterns of any complications will be presented graphically and, if appropriate, a time-to-event analysis (Kaplan-Meier survival analysis) will be used to assess the overall risk and risk within individual classes of important complications (eg, infection).

A detailed statistical analysis plan (SAP) will be agreed on with the Data Management Committee (DMC) at the start of the study. Any subsequent amendments to this initial SAP will be clearly stated and justified. Interim analyses will be performed only where directed by the DMC. The routine statistical analysis will mainly be carried out using R (http://www.r-project.org/) and S-PLUS (http://www.insightful.com/). Results from this trial will also be compared with results from other trials.

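### Pre-injury DRI is collected but enters neither the main nor the adjusted analysis of 6-month DRI: a loss of efficiency of unknown size, not a bias

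*Protocol article*

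**What the plan says.** On collection, the Main RCT summary states: "Baseline demographic data, radiographs and pre-injury functional data using the DRI and the OMAS Questionnaire will be collected". The Outcome measures section says of the DRI: "This data will be collected at baseline, 3, 6 and 12 months postoperatively", and Table 1 lists the DRI at baseline.

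On analysis, the Statistical analysis section makes the comparison of 6-month DRI a two-sided Student t test by intention to treat, with the same test at the other occasions. In addition to that unadjusted analysis it plans "regression analyses to adjust for any imbalance between test treatment groups in patient age or gender", and then extends the linear model with a random effect for recruiting centre. Baseline data in general are to be summarised so that the arms can be compared and participants set against non-participants. No sentence places pre-injury DRI in a model of later DRI.

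The section also promises a detailed statistical analysis plan, which is not at hand.

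**The concern.** The baseline value of an outcome is usually the first covariate to consider when that outcome is analysed. Here it is already being collected, and the article names other adjusters without it. Two things are at stake.

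- **Precision.** If pre-injury DRI predicts 6-month DRI at all, a model that includes it gives a smaller standard error for the treatment effect than the t test, and it accounts for any chance difference between the arms in prior disability.
- **Prespecification.** The wording of the adjusted analysis ties adjustment to imbalance in age or gender. Covariates are better fixed in advance for their expected prognostic value, so that the model does not depend on what the baseline table shows.

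**Working it through.** **Inputs from the protocol**
- Target difference: 8 points (Sample size: "The minimum clinically important difference (MCID) is eight points").
- SD: 20 (Sample size: "The SD of the DRI in our pilot study was approximately 20 points"). The text does not say that this is adjusted for baseline.
- Two-sided 5% level and 90% power (Sample size).
- Equal allocation (Main RCT summary: "Randomisation will be on a 1:1 basis").
- 264 evaluable and 320 randomised, with a 20% allowance for loss (Sample size).

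**Input not in the protocol (assumption)**
- r, the correlation between pre-injury and 6-month DRI. A range from 0 to 0.5 is shown.

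**Step 1: reproduce the stated figure.**
n per arm = 2 × (1.960 + 1.282)² × 20² / 8² = 131.3, rounded up to 132, so 264 in total. This matches Table 2. (The noncentral t distribution gives 266.) The stated size therefore rests on the SD of 20 with no reduction for baseline DRI.

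**Step 2: number analysed if the stated loss occurs.**
320 × 0.80 = 256, or 128 per arm.

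**Step 3: effect of adjustment.**
Residual SD = 20 × √(1 − r²).
SE of the difference = residual SD × √(2/128).
Noncentrality = 8 / SE.
Power is then taken from the noncentral t distribution. The one degree of freedom spent on the covariate makes no visible difference.

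| r (assumed) | Fall in variance | Residual SD | Power, 256 analysed | 95% CI half-width (1.96 × SE) |
|---|---|---|---|---|
| 0 (t test) | 0% | 20.00 | 89.0% | 4.90 |
| 0.1 | 1% | 19.90 | 89.3% | 4.88 |
| 0.2 | 4% | 19.60 | 90.2% | 4.80 |
| 0.3 | 9% | 19.08 | 91.6% | 4.67 |
| 0.4 | 16% | 18.33 | 93.6% | 4.49 |
| 0.5 | 25% | 17.32 | 95.7% | 4.24 |

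Worked line for r = 0.3: SD = 20 × √0.91 = 19.08; SE = 19.08 × √(2/128) = 2.385; noncentrality = 8/2.385 = 3.35; power 91.6%.

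**Step 4: break-even.**
With 256 analysed, power reaches 90% at r of about 0.18. Below that, baseline adjustment alone does not bring it to 90%.

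**Limit of the table.** It compares adjustment for pre-injury DRI with no adjustment. Against the planned model with age and gender, the gain depends on the partial correlation given those variables, which could be smaller than r.

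**The case against.** The strongest case on the other side is that nothing stated is wrong. A two-sample t test is valid in a randomised trial, the sample size was computed for that test, and the design claims no benefit from baseline adjustment. All of that stands, and it is why the point concerns efficiency only.

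It can also be said that covariates belong in the statistical analysis plan, and that an article condenses. This weakens the point without removing it. The article does not leave the matter open: it fixes the main test and names the adjusters. If the unseen plan adds pre-injury DRI, the two documents need to be brought into line.

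The size may also be small. Baseline DRI measures function before the injury, and 0 on the scale is normal function. If many patients score near 0, the score will tell little about recovery. That is plausible but undocumented. The Randomisation section contrasts younger patients with high-energy fractures and older patients with fragility fractures, but in terms of bone quality; it gives no figures on prior disability.

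A reader might extend the point to the Olerud and Molander score and the EQ-5D, which are also recorded for the pre-injury state. The article does not support that. The t test and regressions are set out for DRI, and no model is stated for those two outcomes, so there is no stated choice to criticise. Pre-injury EQ-5D also has a stated use, in generating quality-adjusted life-years in the Health economic analysis section.

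**Conclusion.** The point holds for DRI, as a stated analysis choice with a better alternative that uses data already planned. It is a loss of efficiency. It does not bias the treatment effect and does not invalidate the sample size of 264.

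The size cannot be fixed from the protocol. On the assumptions of SD 20, a difference of 8 and 256 analysed, the gain in power over the t test is 0.3 percentage points at r = 0.1, 1.2 at r = 0.2, 2.6 at r = 0.3 and 6.7 at r = 0.5. Relative to a model that already contains age, it may be less.

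A reader might infer that much information is being discarded, or that any realistic correlation would secure 90% power at 256 analysed. Neither follows. No correlation is documented, and at r = 0.1 power stays below 90%.

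**What to change.** Amend the Statistical analysis section, and the statistical analysis plan to match:

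- Make the primary analysis of 6-month DRI a linear model with treatment, pre-injury DRI as a continuous covariate, age, and the centre effect. Use the same model for DRI at 3 and 12 months.
- State that these covariates are included whatever imbalance is observed, in place of the wording that adjusts for imbalance.
- Keep the Student t test as a supportive analysis.
- Give a simple rule for a missing pre-injury DRI, since collection from every patient is planned but cannot be guaranteed.

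The cost is one degree of freedom and no extra patients or visits. It does change the main analysis stated in the protocol, so it is more than a wording change in the analysis plan, and it should be settled before outcome data are seen by arm.

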## Health economic analysis

A prospective economic evaluation, conducted from a National Health Service and personal social services perspective, will be integrated into the trial design.^25^ The economic evaluation will estimate the difference in the cost of resource inputs used by participants in the two arms of the trial, allowing comparisons to be made between the two surgical treatment options (intramedullary nail vs ‘locking’ plate fixation) for patients with a displaced, extra-articular fracture of the distal tibia, and enabling costs and consequences to be compared. The economic assessment method will, as far as possible, adhere to the recommendations of the NICE Reference Case.^25^ Primary research methods will be followed to estimate the costs of the surgical treatment options, including supplementary devices and rehabilitation inputs. Broader resource utilisation will be captured through two principal sources: (1) routine health service data collection systems and (2) patient questionnaires administered at baseline, and 3, 6 and 12 months postrandomisation. Unit costs for health and social care resources will largely be derived from local and national sources and estimated in line with best practice. Primary research using established accounting methods may also be required to estimate unit costs. Costs will be standardised to current prices where possible. Health-related quality of life will be measured at baseline pre-injury status), and 3, 6 and 12 months postoperation, using the EuroQol EQ-5D measure; responses will be used to generate quality-adjusted life-years (QALYs). The EQ-5D is a short questionnaire that is widely used in economic evaluation; utility weights will be taken from the UK General Population tariff for the EQ-5D. We will, in the first instance, use self-reports of the EuroQol EQ-5 D measure. Where these data are not available, we will estimate health utilities at each time point using mapping equations between the DRI score and EQ-5D health outcomes on the basis of existing data sets held by the trial team. Multiple imputation methods will be used to impute missing data and avoid biases associated with complete case analysis. The results of the economic evaluation will be expressed in terms of incremental cost per QALY gained. We shall use non-parametric bootstrap estimation to derive 95% CIs for mean cost differences between the trial groups and to calculate 95% CIs for incremental cost-effectiveness ratios. A series of sensitivity analyses will be undertaken to explore the implications of uncertainty on the incremental cost-effectiveness ratios and to consider the broader issue of the generalisability of the study results. One such sensitivity analysis will involve adopting a societal perspective for the economic evaluation, which will incorporate direct costs to trial participants, informal care provided by family and friends, and productivity losses. In the baseline analysis, and for each sensitivity analysis, cost-effectiveness acceptability curves will be constructed using the net benefits approach. Heterogeneity in the trial population will be explored by formulating net-benefit values for trial participants from the observed costs and effects, and then constructing a regression model with an intervention variable and covariates such as age, contemporaneous injuries and experience of surgeons in trial participating centres. The magnitude and significance of the coefficients on the interactions between the covariates and the intervention variable will provide estimates of cost-effectiveness of the surgical options by participant subgroup. More extensive economic modelling using decision-analytic methods will extend the target population, time horizon and decision context, drawing on best available information from the literature together with stakeholder consultations to supplement the trial data. Parameter uncertainty in the decision-analytic model will be explored using probabilistic sensitivity analysis. Longer term costs and consequences will be discounted to present values using discount rates recommended for health technology appraisal in the UK.

## Discussion

This pragmatic, multicentre trial is due to deliver results in Spring 2017. Results will be disseminated through peer-reviewed publications, including a National Institute for Health Research Health Technology Assessment monograph. Participants of the trial will receive a lay summary of the trial results.
